#### 7.2.4 Determination of the severity of adverse events

The severity of adverse events is classified as follows:

- (1) Serious
- (2) Non- serious

#### 7.2.5 Actions taken to treat adverse events

Actions taken on subjects to treat adverse events are classified as follows:

- (1) Yes (description: drug therapy, other (details))  
\*If yes, provide detailed information in the section on concomitant medications and therapies in the case report.
- (2) No

#### 7.2.6 Actions taken on the test device

If an adverse event occurs, actions taken on the test device are classified as follows:

- (1) No  
When the use of the test device was not discontinued
- (2) Discontinued  
When the use of the test device was discontinued (the test device was removed)

#### 7.2.7 Outcome of adverse events

The outcomes of adverse events are classified as follows:

- (1) Recovered: The adverse event has disappeared or returned to its original state
- (2) Relieved: The adverse event has not completely recovered, but has almost disappeared or returned to its original state
- (3) Sequelae: The adverse event has recovered to its original state, but sequelae remain
- (4) Unrecovered: The adverse event is ongoing
- (5) Died: The subject died as a result of the adverse event

For adverse events that have not yet recovered as of the end of the observation period for each subject, follow-up will be conducted until recovery or remission occurs as far as possible. However, if the principal investigator or sub-investigator determines that follow-up is not necessary, such as in the case of irreversible events, follow-up may end on the end of the observation period for the subject. In that case,

the reason for determining that follow-up is not necessary should be stated in the comments section of the case report form.

In addition, the causal relationship of adverse events to the test device will be determined on a three-level scale according to the criteria in Table 7.2.7 below, and recorded in the case report form. Based on Table 7.2.7, events that fall into either the category of "Relationship cannot be denied" or "Related" in terms of relevance to the test device are considered to be events for which a causal relationship with the test device cannot be denied. If the event falls into the category of "Not related," the reason for this judgment should be written in the comments section of the case report.

Table 7.2.7 Criteria for determining causal relationship with the test device

|                                   |                                                                |
|-----------------------------------|----------------------------------------------------------------|
| Not related                       | If the relationship with the test device can be clearly denied |
| The relationship cannot be denied | If the relationship with the test device is suspected          |
| Related                           | If the relationship with the test device is clearly recognized |

### 7.3 Malfunctions

#### 7.3.1 Malfunctions

Malfunctions refer to problems with the specifications of the subject device, defects or malfunctions of the subject device, or problems with the procedure. Information on malfunctions that occur during the clinical trial will be collected as needed. In addition, considering the nature of this clinical trial, we will continue to investigate any malfunctions of the biotube even after the test device is removed.

#### 7.3.2 Recording of Malfunction Information

If a malfunction occurs in the study device/biotube, the principal investigator or co-investigator will record the details of the malfunction in the case report. The safety of the malfunction will be determined based on Table 7.3.2.

Table 7.3.2 Fault safety level

|                |                                             |
|----------------|---------------------------------------------|
| Safety level 1 | Affects subjects and surgeons, etc.         |
| Safety level 2 | May affect subjects and surgeons, etc.      |
| Safety level 3 | Does not affect subjects and surgeons, etc. |

#### 7.4 Responses to Adverse Events and Malfunctions

- (1) If the investigator or co-investigator becomes aware that treatment for an adverse event is necessary, he/she shall inform the subject of the event.
- (2) In the event of an adverse event, the investigator or co-investigator shall take appropriate measures, pay attention to ensuring the safety of the subject, and endeavor to determine the cause.
- (3) In principle, the investigator or co-investigator shall continue to monitor the symptoms or abnormal changes in clinical test values as much as possible and confirm the outcome until the event has disappeared or returned to the state before the start of the clinical trial, or until it is determined that the event is not a clinical problem.

#### 7.5 Reporting of serious adverse events and malfunctions that may lead to serious adverse events

If an adverse event occurs in a subject during a clinical trial and the investigator or co-investigator judges the adverse event to be serious, the adverse event will be handled according to the following procedures.

- (1) Report from the investigator to the head of the clinical trial institution and the coordinating investigator  
The investigator shall report the adverse event information to the head of the clinical trial institution as soon as possible, regardless of causality, and shall also report it to the coordinating investigator.
- (2) Notification by the coordinating investigator to the investigators and investigational device providers of each medical institution  
The coordinating investigator shall confirm the contents of the adverse event report received from the investigator and notify the investigators and investigational device providers of each other medical institution of the adverse event information.
- (3) Discussion between the Principal Investigator and the Coordinating Investigator  
The Principal Investigator at each medical institution shall review the report received from the Coordinating Investigator, consult with the Principal Investigator as necessary, and report his/her opinion as the Principal Investigator (including the need to report to the Minister of Health, Labour and Welfare) to the Coordinating Investigator.
- (4) Convening an Efficacy and Safety Evaluation Committee  
If the Coordinating Investigator determines that the adverse event is subject to reporting under Article 273 of the Enforcement Regulations of the Pharmaceuticals and Medical Devices Act, he/she shall convene an Efficacy and Safety Evaluation Committee and request a decision on whether or not to continue the clinical trial.

If the Efficacy and Safety Evaluation Committee determines whether or not to continue the clinical trial, it shall notify the Coordinating Investigator, who shall notify the Principal Investigator.

(5) Report to the Minister of Health, Labour and Welfare

If the principal investigator determines that the defect or other problem should be reported to the Minister of Health, Labour and Welfare as stipulated in the "Act on Ensuring Quality, Efficacy and Safety of Pharmaceuticals, Medical Devices, etc." and its Enforcement Regulations, the coordinating investigator will prepare a report in the designated format and submit it to the PMDA.

(6) Report to the head of the medical institution conducting the study

When a serious adverse event that occurred at another medical institution is reported to the Minister of Health, Labour and Welfare, the principal investigator shall report the contents of the report in (5) obtained from the coordinating investigator to the head of the medical institution as soon as possible.

(7) Response when additional information is obtained

When the principal investigator of the medical institution where the adverse event occurred obtains additional information on the adverse event, he/she shall report it to the head of the medical institution as soon as possible and also report it to the coordinating investigator and the investigational device provider. The handling of the additional information shall conform to the procedures in (1) to (6) above, and shall report it to the PMDA if necessary.

## 7.6 Provision of new information

If the investigator obtains any information that may adversely affect the safety of the subjects, affect the conduct of the clinical trial, or change the approval of the IRB or other such organization regarding the continuation of the clinical trial, he/she shall promptly report this in writing to the head of the medical institution conducting the trial, and shall promptly revise the explanatory document if necessary. The investigator or co-investigator shall notify the subject of this and ensure appropriate treatment and follow-up procedures.

## 8. Efficacy evaluation

### 8.1 Primary evaluation item

Ability of forming biotubes by the test device

When the biotube is removed from the core and inserted into the straightening rod, the presence or absence of abnormalities such as inflammation is checked and the formation

state is evaluated visually. After soaking in alcohol, the total length of the biotube is measured while it is inserted into the straightening rod. If the biotube is formed in segments, the length of each segment and the total length are measured. In addition, the thickness and uniformity of the tissue are visually examined. The straightening rod is removed, and the lumen is pressurized with saline using a syringe to check for damage and leakage. A portion is taken and the breaking strength is measured using a tensile tester. Histopathological observation is performed at a later date to examine the thickness, inflammation, and collagen structure. Note that this evaluation item is intended to evaluate the quality of the formed biotube from multiple perspectives, but in each case, if bypass surgery can be performed using only the biotube as a bypass graft (including cases where fragments of the biotube are used together), this evaluation item is considered to be "achieved."

## 8.2 Secondary Evaluation Items

The following evaluation items (1) to (8) will be evaluated secondary to the above.

### (1) Procedural success regarding implantation and removal of the test device

At the time of implantation, the subcutaneous pocket will be visually evaluated to ensure that it is large enough to create a sufficient size subcutaneous pocket, that the test device can be inserted without damaging or disintegrating the device, and that the wound can be closed while controlling subcutaneous bleeding. During the implantation period, the skin will be visually evaluated to ensure that there are no abnormalities such as hematoma formation or accumulation of exudate. At the time of removal, the degree of adhesion between the test device and the surrounding tissue will be confirmed, and it will be visually evaluated that the test device can be removed without damaging or disintegrating the device while controlling bleeding.

### (2) Procedural success of bypass surgery including peripheral anastomosis using a biotube formed by the test device

It will be visually evaluated whether the biotube can be sutured without damage or cutting using the same technique as a bypass surgery using a normal vein. It will be visually evaluated whether bleeding from the anastomosis site can be controlled, and there is no blood leakage, tearing, or swelling from the biotube wall. After releasing the vascular clamp, pulsatile blood flow is confirmed and the flow rate is measured with a flowmeter to evaluate peripheral revascularization. Note that "technical success" in this evaluation item refers to cases where bypass surgery was performed using only the biotube as a bypass graft (including cases where fragments of the biotube were joined together), and does not include cases where bypass surgery was performed by joining an autologous vein or an artificial blood vessel.

(3) Patency of the biotube at 12 weeks after implantation

During the follow-up period, blood flow in the biotube is evaluated by lower limb arterial echocardiography. If possible, the shape of the biotube is observed by lower limb CT angiography or lower limb arteriography to evaluate the presence or absence of abnormalities such as stenosis or swelling.

(4) Improvement of symptoms (improvement of ischemic pain, improvement of wounds)

The pain improvement rate, wound improvement rate, wound area reduction rate, and granulation formation rate are evaluated at the time of eligibility confirmation, at the time of biotube implantation, and 1, 4, 8, and 12 weeks after biotube implantation. In addition, the Wiffl score is also evaluated at the time of eligibility confirmation, and 1, 4, 8, and 12 weeks after biotube implantation.

(5) Avoidance of major amputation

The avoidance rate of major amputation of the target lower limb during the follow-up period will be examined.

(6) Implementation rate of additional treatment during implantation of the study device and after biotube implantation

The rate of revascularization other than bypass surgery using the biotube will be evaluated from implantation of the study device to the end of the follow-up period.

(7) QOL during implantation of the study device and after implantation of the biotube

The results of a questionnaire conducted approximately 6 weeks after implantation of the study device will be used to evaluate the presence or absence of discomfort at the implantation site of the study device and the presence or absence of impact on daily life. In addition, the results of a questionnaire conducted at the end of the follow-up period will be used to evaluate the QOL after biotube implantation.

(8) Bypass graft diameter after bypass surgery

During the follow-up period, the diameter of the biotube used in the bypass surgery (including artificial blood vessels or autologous veins, if used) will be investigated and evaluated over time by lower limb arterial echocardiography.

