## (2) Safety evaluation items

- ① The occurrence of inflammation, tumor formation, or death that cannot be ruled out as being related to the test device during the period of subcutaneous implantation of the test device
- ② Biocompatibility of the implanted biotube (inflammation, rejection, tumor formation, etc.)
- ③ Burst of implanted biotubes
- ④ Deaths related to implanted biotubes cannot be ruled out
- ⑤ Deaths within 12 weeks after implantation of biotubes
- ⑥ Other adverse events and malfunctions

[Rationale for setting]

Since the medical device is implanted in the body, it is necessary to carefully check whether it has any adverse effects on the body. In addition, the formed biotube is made of the patient's own tissue, but since the tissue formed subcutaneously will be used as blood vessels in another part of the body, it is

necessary to confirm that it can be safely implanted without any malfunctions and functions as a blood vessel.

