- 13) The biotube is removed from the core and washed with physiological saline.
- 14) A straightening rod is inserted into the lumen of the biotube and it is immersed in alcohol (70%) in an immersion dish for 30 minutes.
- 15) The biotube is washed again with saline, and visually inspected to ensure that there are no tears, defects, or significant deviations in wall thickness
- 16) Store in heparinized saline until use for transplantation.
- 17) As with bypass surgery using an autologous vein graft, load saline into the inside of the biotube with a syringe to confirm that there are no leaks,

and use a pressure monitor to check for pressure resistance (presence or absence of swelling or rupture under a pressure load of 200 mmHg). Also, use a tensile tester to measure the maximum strength and confirm that it meets the standard strength (5 N).

The biotube prepared using steps 1) to 17) above is transplanted into the subject's lower limb as a substitute blood vessel, in the same way as an autologous vein graft. If the investigational device cannot be removed and the biotube implanted on the same day due to the subject's general condition or other reasons, the prepared biotube may be temporarily stored. When temporarily storing, the biotube should be immersed in 10% alcohol while maintaining a sterile state, sealed, and stored at room temperature (if the prepared biotube is in fragments, it should be stored as is). In this case, the temporary storage period should be a maximum of 4 weeks, and the biotube implantation should be performed within 4 weeks of the investigational device removal. In addition, the investigator should make appropriate preparations before the start of the clinical trial, such as securing a storage location and creating storage procedures, to prevent loss or mix-up during temporary storage.

[Rationale for setting]

The results of non-clinical trials have confirmed that the shape and strength of the BioTube did not change significantly for six months at room temperature. From the above, it has been confirmed that temporary storage is possible, but in order to prevent the condition from worsening, it is preferable to transplant the BioTube as soon as possible, and at the latest within four weeks after removal of the test device. Therefore, the temporary storage period was set at a maximum of four weeks (at room temperature).

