##### (2) Postponement or Cancellation of Biotube Transplantation (Bypass Surgery)

In the following cases, biotube transplantation (bypass surgery) will be canceled and the clinical trial will be discontinued. Even if the trial is discontinued, the biotube will be evaluated according to the procedure specified in "6.4.2 (4) Evaluation of Biotubes that were not Transplanted".

- Cases in which no biotube of usable quality was formed.
- Cases in which major amputation of the target limb was necessary due to wound infection causing the extent of necrosis to increase.
- Cases in which the patient's general condition makes it difficult to perform biotube transplantation due to the occurrence of adverse events, etc. However, temporary postponement rather than cancellation is permitted only when the principal investigator or co-investigator determines that biotube transplantation can be considered within the allowable period specified in the clinical trial protocol.

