#### 6.4.4 Implantation period of the test device and follow-up period

Implantation period of the test device: 4 to 24 weeks (in principle, 8 weeks or more)

Post-observation period: up to 12 weeks after implantation of the biotube

In addition, this period includes the pre-observation period from consent acquisition to registration (up to 8 days) and the follow-up period for adverse events (if adverse events that require follow-up occur).

[Rationale for setting]

The longer the implantation period, the more the tissue formation of the biotube progresses, but to avoid excessive worsening of the symptoms of lower limb ischemia, it is desirable to perform bypass surgery as soon as possible. Therefore, although it depends on the symptoms, the implantation period was set to about 2 months (8 weeks) in principle to ensure the formation of the biotube. In addition, since it was confirmed in non-clinical studies that the biotube could be formed after one month of implantation, it was considered acceptable to perform removal and bypass surgery even if the implantation period was between four and eight weeks if significant progression of ischemia was observed after implantation, and therefore the shortest implantation period was set at four weeks.

In addition, since symptoms usually improve around three months after implantation when bypass surgery is performed using an autologous vein, and since the results of non-clinical studies suggest that the implanted biotube is generally replaced by autologous tissue around three months after implantation, the observation period after implantation of the biotube was set at 12 weeks.

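### Avoidance of major amputation (Protocol 8.2 (5)) is counted only after biotube bypass, so it describes limb salvage conditional on reaching bypass, not salvage in all implanted subjects

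*Protocol*

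**What the plan says.** The amputation endpoint in Protocol 8.2 (5) reads: "The avoidance rate of major amputation of the target lower limb during the follow-up period will be examined". It names neither a start date nor a denominator.

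The protocol gives no formal definition of the follow-up period. Section 6.4.4, whose heading pairs the device implantation period with the follow-up period, lists two phases: device implantation of 4 to 24 weeks (as a rule at least 8), and "Post-observation period: up to 12 weeks after implantation of the biotube". Section 6.4.2 (1) adds a possible gap between the two: "the temporary storage period should be a maximum of 4 weeks".

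Neighbouring endpoints use the term for the time when the graft is in place. Section 8.2 (3) says "During the follow-up period, blood flow in the biotube is evaluated by lower limb arterial echocardiography", and 8.2 (8) tracks graft diameter over the same period. Section 8.2 (6), on additional revascularization, has a wider window: the rate "will be evaluated from implantation of the study device to the end of the follow-up period".

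Among the reasons for cancelling bypass and discontinuing the subject, 6.4.3 (2) lists: "Cases in which major amputation of the target limb was necessary due to wound infection causing the extent of necrosis to increase".

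On deaths, 3.2 (2) has a named all-cause item that starts at bypass, "Deaths within 12 weeks after implantation of biotubes". Deaths in the device period are named separately only where a relation to the device cannot be excluded. A final item takes in all other adverse events.

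**The concern.** A patient without a usable vein can receive a biotube only after carrying the device for weeks with an ischaemic limb. Section 6.4.4 itself recognises that ischaemia may worsen in that time, and 1.5.1 (3) warns that rapid progression may rule out bypass after BTM1 has been implanted. A limb lost in this interval is an outcome of the course of treatment the patient entered, yet endpoint (5) does not see it.

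This matters because 1.5.2 puts avoidance of major amputation first among the expected benefits, and the rationale in 3.2 asks whether amputation can be avoided. A salvage rate from this trial is likely to be read as the result for patients who had BTM1 implanted. As worded, it is the result for those who still had a limb to bypass. With about 12 subjects, one or two limbs change the impression materially.

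**Working it through.** There is no figure in the plan to reproduce. The target of 12 in 9.5 rests on device sizes, implantation sites and feasibility, and no amputation rate is given anywhere.

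**1. Where the window starts.** Section 6.4.4 separates device implantation from the 12 weeks after bypass. Items (3) and (8) of 8.2 can be observed only with a graft in place. Item (6) has to name device implantation as its start in order to include the wait, and item (5) has no such words. All four point to a start at bypass for item (5).

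**2. What falls outside it.** Under 6.4.3 (2), a major amputation before bypass cancels the operation and ends participation. The event therefore precedes the window. None of the other seven secondary endpoints counts it.

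**3. Share of time omitted.** For a wait of w weeks, the share of the time from implantation to week 12 after bypass that is left out is w/(w + 12).

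- w = 4: 4/16 = 25%
- w = 8: 8/20 = 40%
- w = 24: 24/36 = 67%
- w = 28 (24 weeks plus 4 weeks of storage): 28/40 = 70%

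**4. Effect on the rate.** Assume 12 implanted subjects, k limbs lost before bypass, a lost afterwards, and everyone else bypassed. The values of k and a are illustrative.

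| k | a | All implanted, from implantation: (12−k−a)/12 | Bypassed only: (12−k−a)/(12−k) | FAS denominator, follow-up events only: (12−a)/12 |
|---|---|---|---|---|
| 1 | 0 | 11/12 = 91.7% | 11/11 = 100% | 12/12 = 100% |
| 2 | 0 | 10/12 = 83.3% | 10/10 = 100% | 12/12 = 100% |
| 3 | 0 | 9/12 = 75.0% | 9/9 = 100% | 12/12 = 100% |
| 1 | 1 | 10/12 = 83.3% | 10/11 = 90.9% | 11/12 = 91.7% |
| 2 | 1 | 9/12 = 75.0% | 9/10 = 90.0% | 11/12 = 91.7% |
| 3 | 1 | 8/12 = 66.7% | 8/9 = 88.9% | 11/12 = 91.7% |

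Each pre-bypass loss lowers the all-implanted rate by 1/12 = 8.3 points. Under the bypassed-only reading the subject disappears. Under the FAS reading the lost limb counts as saved.

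**5. Chance that the issue arises.** If each subject independently has probability p of losing the limb before bypass, the chance of at least one loss among 12 is 1 − (1 − p)^12. For assumed p of 5%, 10%, 20% and 30%, this is 46%, 72%, 93% and 99%.

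**6. A limit on step 4.** Subjects may also miss bypass with the limb intact, for example when it is not needed at 24 weeks (4.4 (7)). If m such subjects exist and B are bypassed, the bypassed-only rate overstates the all-implanted rate when a/B < k/(k + m). This always holds with a = 0 and k ≥ 1, but not for every combination. The FAS reading overstates by k/12 regardless of m.

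**The case against.** The strongest reply has four parts.

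- **The denominator is open.** Section 8.2 (5) names none. The FAS in 9.1 does not remove a subject merely for losing a limb before bypass, and discontinued cases go to case review. An analyst could score such a subject as a failure in the FAS and reach the all-implanted figure. This stands against any claim that 9/10, or any other single figure, is the rate as written. It does not remove the point, because choosing a denominator does not bring back an event that the protocol's own window leaves out.
- **The stated purpose is bypass with a biotube.** A post-bypass rate suits that purpose, and the title of item (6) expressly covers the device period while that of item (5) does not. So the two windows are not a contradiction, and the post-bypass rate deserves to be kept. It does not answer the question about implanted subjects.
- **The events are recorded.** Adverse events are collected from device implantation (6.5.1 (21), 7.2.1), and discontinued subjects are examined (6.5.2). This is correct: no data are lost, only the summary is incomplete. A reader might infer that unrelated deaths during the wait go unreported, but the item for other adverse events covers them.
- **The size is illustrative.** This is also correct. A reader might take the 25% to 67% of omitted time as the share of amputations missed. That would need a constant hazard before and after bypass, which the protocol does not support.

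A reader might also call this immortal-time bias. That label does not fit: if clock and denominator both start at bypass, no immortal time is counted, and the rate is simply conditional on bypass.

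**Conclusion.** The point holds as a matter of interpretation. Endpoint (5) measures limb salvage given that bypass was reached, while the protocol foresees limb loss before that and no efficacy item counts it. If any limb is lost during the wait, the rate would overstate salvage among all implanted subjects, either by dropping the subject or by counting the limb as saved, subject to the limit in step 6 of the working.

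The conclusion rests on reading the follow-up period as post-bypass. The term is undefined and is used elsewhere for adverse-event follow-up, but 6.4.4 and the three neighbouring endpoints agree on this sense. The 8.3 points per limb assumes 12 implanted subjects. The total effect is unknown, and is zero if no limb is lost before bypass.

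This is one of eight secondary endpoints in an exploratory single-arm trial. No test or success threshold is attached to it, and the interim analysis in 9.4 does not use it. The trial's primary conclusion is not at risk.

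**What to change.** In 8.2 (5), adopt the start already used in 8.2 (6). Count major amputation of the target limb from BTM1 implantation to the end of follow-up or discontinuation, in all implanted subjects, with a pre-bypass major amputation as an event. Keep the post-bypass rate as a supportive figure, labelled as conditional on bypass, and show the number of limbs lost before bypass beside it. Define the follow-up period once, so that it cannot be confused with adverse-event follow-up.

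A named line for all-cause death from BTM1 implantation in 3.2 (2) and 9.3 would be convenient but is optional, since those deaths are already captured as adverse events.

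The cost is protocol and analysis-plan wording only; no new data collection is needed. The downside is a possibly less favourable salvage figure. The change should be made before results are known, because at this sample size the choice of window can visibly move the rate.
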